### Secondary endpoints and measures

#### Degree of MD in the IMF (patchy vs. confluent and area of MD)

Dimensions of any MD will be measured by using a ruler on the skin by trained staff blind to the treatment arm.A patch of MD is defined as a single spot up to 2 cm in its largest dimension. When patches exist, the dimensions of the overall patchy area and the dimensions of the largest patch will be recorded.When multiple patches have become confluent or a single patch is greater than 2 cm in its longest dimension, these areas will defined as confluent and the dimensions will be recorded.

#### Overall NCI CTCAE breast skin assessment

The overall breast skin assessment will be scored using the NCI CTCAE V4.0 criteria for radiation dermatitis by the blinded study radiation therapist.

#### Treatment planning dose-volume statistics

The following dose-volume measurements will be acquired:◦ V20 Gy ipsilateral lung◦ V25 Gy heart◦ V105% body◦ V50% body◦ Breast separation (cm)The measurements will be reported as relative volume (% of structure volume), absolute volume (cm^3^), relative dose (% of prescribed dose), and absolute dose (Gy).Breast separation (cm) will be measured from beam entry to beam exit at the posterior beam edge at mid-breast level.

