## Methods/Design

### Objectives

The primary objective of this study is to determine whether CARA V3.0 can reduce the incidence of moist desquamation in the IMF for patients with large or pendulous breasts undergoing breast RT in the supine position.

The secondary objectives of the study are as follows:To assess whether the severity of MD in the IMF can be reduced using CARA V3.0.To assess whether overall breast skin reaction scores can be reduced using CARA V3.0.To assess if CARA V3.0 reduces the volume of ipsilateral lung receiving 20 Gy or more (V20Gy).To assess if CARA V3.0 can reduce or maintain the volume of heart receiving 25 Gy or more (V25Gy) for left breast patients.To assess if CARA V3.0 can reduce the volume of body receiving greater than 50% (V50%) and greater than 105% (V105%) of the prescribed dose.To determine a dose-area parameter that is predictive of MD.To compare workflow and breast position reproducibility between the two study arms.To compare the PROs for quality of life measures and comfort during treatment setup between the two study arms.To compare radiation therapist experience between the two study arms.

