### Interventions

#### Radiation therapy

For both study arms, breast RT protocols currently in use at the treating centres will be used. Dose fractionation schedules include 26 Gy in 5 daily fractions, 42.5 Gy in 16 daily fractions, 40 Gy in 15 daily fractions, 45 Gy in 25 daily fractions, and 50 Gy in 25 or 28 daily fractions. The extended fractionation schedules are generally reserved for patients with a large separation (> 24 cm) or significant post-operative changes. Partial breast treatments are acceptable if the inferior breast skin is included in the treated volume.

The treatment delivery will generally consist of a tangent pair of photon fields with or without internal mammary, supraclavicular, and/or axillary nodal fields. Combinations of 6 MV, 10 MV, 15 MV or 18 MV photons are permitted as required to meet planning dose constraints. Volumetric modulated arc therapy (VMAT) is currently under consideration.

Additional boost radiation to the tumour bed may be prescribed at the discretion of the radiation oncologist. Boost may be delivered using MV photons or electrons before, during, or following breast RT.

In both arms, patients will be planned and treated in the supine position on an angled breast board. In addition, patients must be indexed to the breast board and the breast board must be indexed to the treatment couch. Deep inspiration breath hold (DIBH) for left breast patients may be used to reduce dose to the heart [34] in both study arms. Standard skin care instructions will be utilized.

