#### Treatment planning and dose constraints

Treatment planning will be performed for both study arms according to current standard of care using the Varian Eclipse AAA algorithm (V13.6) or equivalent, as assessed at credentialing or during the trial if system upgrades occur. Correction for lung inhomogeneity will be used.

PTV, OTV or Breast_Eval coverage by the 95% isodose surface is required. The dose homogeneity objective is V105% < 2% of the OTV. Beam energy may be adjusted as required to achieve PTV coverage and homogeneity criteria, however PTV coverage will take priority over dose homogeneity if the latter cannot be met. For treatments of 15, 16, 25, or 28 fractions, ipsilateral lung V20 Gy shall be ≤ 15% of the lung volume (≤ 35% if regional nodes are treated) and V25 Gy heart shall be ≤ 5% of the heart volume. For 26 Gy in 5 fraction treatments, ipsilateral lung V8 Gy shall be ≤ 15% of the ipsilateral lung volume, heart V1.5 Gy shall be ≤ 30% and heart V7 Gy shall be ≤ 5% of the heart volume. Sliding window or field-in-field (step and shoot) IMRT may be used as available at the treating center.

All treatment plans in this study will be approved by the treating oncologists and designated physicists at each site, including a quality assurance check on all contours. All constraint violations will be noted on the planning data form.

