#### Statistical methods – secondary outcomes

The eight secondary endpoints will be compared between the two study arms as follows:Degree of MD in the IMF: Peak measured area (cm^2^) of patchy MD and confluent MD will be compared where data is available. It is anticipated that a good proportion of patients will have no MD and hence a measured area of zero. Thus, we will divide the outcome into four categories, the first being zero and the other three will be equal sized groups based on their area score. We will then use the linear trend chi-square test to determine whether the groups differ in their distribution of scores.Peak (worst) modified NCI CTCAE scores for radiation dermatitis will be compared using the chi-square test for trend [36].Dose-volume statistics: values for heart, lung, and body will be compared using the Mann–Whitney U test.Dose-area statistics (*in-vivo* dosimetry): Measured skin dose-area statistics will be compared within both study arms. The measured skin dose-area data for patients developing MD in the location where the dose was measured will be compared with that of patients not developing MD in that location to determine if a dose-area metric predictive of MD can be found for either arm.PRO: The peak (worst) PRO breast symptom scores will be compared using a between-groups t-test, or if data do not conform to test assumptions, the non-parametric Mann–Whitney U test. The requirement for steroid cream and analgesics will be compared using the chi-square test, or Fisher’s exact test, if appropriate.Clinical workflow: Time for patient setup will be compared between study arms using a between groups t-test.Reproducibility of patient setup, as assessed by variation in surgical clip positions measured on imaging will be compared between study arms using the F-test.Therapist satisfaction: Therapist satisfaction with the setup procedure as measured by the questionnaires will be compared using a linear trend chi-squared test.

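### Lung V20Gy and heart V25Gy are applied to all schedules, but on 26 Gy in 5 they sit at 77% and 96% of the prescription, so five-fraction values are not comparable with the rest

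*Protocol article*

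**What the plan says.** **Objectives.** The lung objective is a reduction in ipsilateral lung V20Gy, for all patients. The heart objective is to "reduce or maintain the volume of heart receiving 25 Gy or more (V25Gy) for left breast patients".

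**Treatment planning dose-volume statistics.** The endpoint list gives "V20 Gy ipsilateral lung" and heart V25Gy, without reference to schedule. The two body endpoints in the same list, V50% and V105%, are percentages of the prescription.

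**Radiation therapy.** "Dose fractionation schedules include 26 Gy in 5 daily fractions", and also 40 Gy in 15, 42.5 Gy in 16, 45 Gy in 25, and 50 Gy in 25 or 28.

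**Treatment planning and dose constraints.** The V20Gy lung and V25Gy heart limits are stated for 15, 16, 25 or 28 fractions only. The shorter schedule has its own: "For 26 Gy in 5 fraction treatments, ipsilateral lung V8 Gy shall be ≤ 15% of the ipsilateral lung volume", with heart V1.5Gy at most 30% and heart V7Gy at most 5%.

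**Statistical methods – secondary outcomes.** For dose-volume statistics, "values for heart, lung, and body will be compared" by the Mann–Whitney U test. No stratification or subgrouping by schedule is stated.

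**Randomization procedure and tracking.** Fractionation is a stratification factor, with presence of a skin fold and centre.

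**The concern.** An absolute-dose threshold describes a different part of the dose distribution when the prescription changes. V25Gy in a 50 Gy plan is the volume receiving at least half the prescription; in a 26 Gy plan it is the volume receiving almost the full prescription. The planning section recognises this and changes thresholds for five fractions. The endpoint list and its test do not.

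If the endpoint is analysed as written, five-fraction patients enter the ranking on a scale of their own. For the heart they may form a block of low, possibly tied values that carries little information about the device. For the lung they are expected to be shifted towards lower values. A real effect of the device on heart or lung exposure could then be missed, and a null result would say little about five-fraction patients. The heart objective is partly to show that exposure is maintained, so an insensitive metric could also make apparent equality look more reassuring than it is.

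**Working it through.** The protocol gives no power or sample-size figure for the dose-volume endpoints, so there is none to reproduce. The check has three parts.

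**1. Threshold as a share of prescription.** Formula: threshold dose ÷ prescribed dose.

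| Prescription | 20 Gy (lung) | 25 Gy (heart) |
|---|---|---|
| 26 Gy in 5 | 20/26 = 76.9% | 25/26 = 96.2% |
| 40 Gy in 15 | 20/40 = 50.0% | 25/40 = 62.5% |
| 42.5 Gy in 16 | 20/42.5 = 47.1% | 25/42.5 = 58.8% |
| 45 Gy in 25 | 20/45 = 44.4% | 25/45 = 55.6% |
| 50 Gy in 25 or 28 | 20/50 = 40.0% | 25/50 = 50.0% |

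The protocol's own five-fraction thresholds are far lower: 8/26 = 30.8% for lung, and 7/26 = 26.9% and 1.5/26 = 5.8% for heart.

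**2. What the document implies about five-fraction values.** The volume receiving at least a given dose cannot rise as the dose rises. A plan that meets the five-fraction limits therefore has:

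- heart V25Gy ≤ V7Gy ≤ 5%
- lung V20Gy ≤ V8Gy ≤ 15%

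These are upper bounds. Constraint violations are allowed and recorded, so individual plans may exceed them.

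**3. Illustration of lost sensitivity, heart.** Every input here is assumed: 55 left-sided patients per arm; V25Gy normal with mean 2% and SD 2%, negative values set to zero; a device shift of 1.1 points; and V25Gy of zero in all five-fraction plans, which is the extreme case. Power is for a two-sided 5% Mann–Whitney test.

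| Five-fraction share | Pooled, equal share in both arms | Pooled, share varying by chance | Longer schedules only |
|---|---|---|---|
| 0% | about 79% | – | – |
| 25% | about 46% | about 48% | about 66% |
| 50% | about 11% | about 21% | about 47% |
| 75% | about 1% | about 10% | about 27% |

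Part of the fall comes from having fewer informative patients, as the last column shows. The rest comes from adding tied values. Under these assumptions, pooling does worse than leaving the five-fraction patients out. If the longer-schedule values are kept well clear of zero instead, with an effect of 0.55 SD, the pooled figures at equal shares are lower still: about 25% at a 25% share and about 0% at a 50% share.

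**Lung.** Assume 110 patients per arm, an effect of 0.39 SD in every schedule, and five-fraction values shifted down by 2 SD. Pooled power is then about 81%, 57%, 47% and 59% at shares of 0, 25, 50 and 75%. The loss is largest when the two groups are of similar size.

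**The case against.** **The analysis plan may stratify.** The document is a condensed article, the analysis plan is not shown, and the text does not use the word pooled. A stratified secondary test could be specified elsewhere. That stands for the test, but not for the metric, which the objectives and the endpoint list fix positively. Stratifying alone does not make V25Gy informative in a stratum where it lies at 96% of the prescription.

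**Relative dose will also be reported.** The endpoint section does promise results as a percentage of prescribed dose as well as in Gy. This softens the point, but it does not define a schedule-specific threshold for lung or heart.

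**Stronger readings that the document does not support.**

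- A reader might infer that five-fraction heart V25Gy is almost certainly near zero. That is plausible in an organ being spared, but no dose-volume data are given. The document supports only the 5% bound for a compliant plan, which equals the V25Gy ceiling on the longer schedules. Breath hold is allowed in both arms, so low values need not be peculiar to five fractions.
- A reader might apply the heart point to every patient. The heart objective covers left breast patients only.
- A reader might infer bias between arms. Stratification by fractionation rules out a systematic difference in schedule mix. Laterality is not a stratum, so exact balance among left-sided patients is not assured, but any imbalance would be by chance.
- A reader might quote a definite power loss. The shares, means, SDs and shifts are all assumed, and the lowest figures need exact balance between arms.

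**Conclusion.** The mismatch holds. It is internal to the protocol: the planning section confines V20Gy and V25Gy to 15–28 fractions, while the objectives, the endpoint list and the test apply them to every schedule. The ratios are exact: 77% and 96% of the prescription on 26 Gy in 5, against 40–50% and 50–62.5% otherwise. Lung values (all patients) and heart values (left breast patients) from five-fraction plans are therefore not comparable with the others.

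The harm is reduced sensitivity and a result that mixes two quantities, in secondary endpoints. The primary endpoint, the sample size and the interim rule are unaffected. The size of the loss cannot be stated without the five-fraction share and the variability on each schedule. It ranges from none, if few patients receive five fractions, to severe for the heart, if many do and their values are tied. This should be corrected before the dose-volume data are analysed.

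**What to change.** Reconcile the objectives, the endpoint list and the secondary analysis with the planning section:

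1. Define the analysed lung and heart metric by schedule. Keep V20Gy and V25Gy for 15–28 fractions. For five fractions, use thresholds that the protocol already evaluates. Two are listed for the heart, and the trial team should choose between them and give the reason before looking at the data by arm. Alternatively, define both metrics as a fixed percentage of prescription, as the body endpoints already are.
2. Compare arms with a rank test stratified by five versus 15–28 fractions (van Elteren), with the heart comparison in left breast patients, and report each stratum.
3. Do not rank V20Gy or V25Gy across the two groups together.

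This concerns measurement and analysis only; no planning limit or treatment changes. The cost is a few sentences and some extra fields on the planning data form. The five-fraction values already have to be calculated to check the constraints, and fractionation is already recorded and stratified on. The coordinating institution retains its plans in its clinical database, so values for patients already enrolled there should be recoverable; other sites would have to supply theirs. With schedule-specific thresholds, the small downside is a combined rank test over two metrics in place of a single V20Gy or V25Gy comparison.

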#### Dose-area statistics measured *in-vivo* on breast skin

Skin dose will be measured using GafChromic™ film in contact with the skin surface and analyzed using FilmQAPro™ software. Film dosimetry will be performed at the central coordinating centre on one to three treatment fractions depending on the prescribed dose fractionation schedule.In the experimental arm, the film will line the CARA support in contact with the breast.In the control arm, when achievable, the film will be placed along the chest wall with the superior edge of the film along the infra-mammary breast crease. This will place the film in the skin fold when a skin fold is present.

#### Patient-reported outcomes

The PRO questionnaire will be provided on tablets in the clinic by the study radiation therapist on the days that the patient is being assessed and by e-mail post-RT.Secondary patient-reported outcomes include severity of fatigue, pain, sleep interruption, activity interruption, comfort during the treatment procedure, and use of steroid cream or analgesics.

#### Clinical workflow

Simulations and treatments will be timed as workflow measures. These times will be measured by the study therapist from the point at which the patient enters the simulation or treatment room for the procedure until the patient exits the room post procedure.

#### Breast position reproducibility

The position (Cartesian coordinates relative to a reference point) of anatomical features and surgical clip positions on kV imaging, MV imaging and cone-beam CT (CBCT) images taken at treatment will be compared.

#### Therapist experience

Therapist experience with the treatment setup procedure will be collected using a purpose-built questionnaire for this study [see Additional file 2] to be completed by one or more therapists during the last week of treatment for each patient.

### Patient population

This study is designed for patients having large or pendulous breasts resulting in IMF and/or lateral breast ptosis. The oncologist or radiation therapist will use an eligibility checklist to pre-screen for potential participants. Patients receiving nodal RT are eligible assuming the inclusion criteria are met. Enrolment in other studies at the same time is permitted at the discretion of the treating radiation oncologist. Waivers to eligibility criteria are not permitted.

Patient participation will be required for seven weeks after the start of breast RT with PRO questionnaires to be completed weekly, starting the last week of treatment and through to the duration of this seven-week period. Follow-up assessments with staff may be done in the clinic or remotely (e.g. Tele-Health, Zoom, phone, e-mail).

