Interpretation of study results with respect to MD is made challenging by the fact that in standard scoring systems, MD appears in both grades 2 and 3 (e.g., Radiation Therapy Oncology Group (RTOG) and National Cancer Institute – Common Terminology Criteria for Adverse Events (NCI CTCAE V5.0)). In addition, many studies do not document BMI or the presence of skin folds, and many studies do not monitor skin toxicity out to two weeks post-treatment when at least 10% of skin reactions peak [8] for standard fractionation schedules, which can result in under-reporting of MD.

In breast RT, skin dose depends on factors including the planning technique, dose constraints, dose prescription, and beam energy. Patients having skin folds during treatment are expected to develop MD in the fold because delivering the prescribed breast dose involves the skin fold dose reaching over 95% of the prescription dose, as it lies within the treatment volume. The risk of MD has also been linked with the volume of the treated breast receiving 105% or more of the prescribed dose (breast V105%) [21–23].

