### Data collection

#### Baseline assessment

Data collection activities are shown in Table 1. Patients will have a baseline assessment prior to the first treatment. Patient height and weight, BMI, age, smoking status, RT prescription (including boost), adjuvant chemotherapy, brassiere size (band and cup size), IMF skin fold depth in treatment position, and presence of other skin folds will be recorded. The skin will also be assessed at baseline for any pre-existing conditions such as erythema, telangiectasia, desquamation, or infection. At CT simulation, a baseline photograph of the IMF skin will be acquired as well as a photo of the patient in treatment position. A PRO questionnaire is also collected at baseline.

**Table 1 Tab1:** Schedule of activities and data collection

**Study Activity**	**New patient appointment with radiation oncologist**	**Prior to CT simulation**	**Prior to first treatment**	**Weekly during Breast RT**	**Post-RT weekly to 7 weeks from start of breast RT**
Introduction to study	**X**				
Inclusion/exclusion criteria screening	**X**	**X**			
Informed consent obtained		**X**			
Enrollment and randomization		**X**			
Baseline assessment			**X**		
Patient-reported outcome questionnaire			**X**	**X**	**X**
Skin assessment performed by staff			**X**	**Last week of RT, or for five-day fractionation, last day of RT**	**Optional per patient preference**
Skin dose measurement				**Up to three times per patient; optional for sites other than the coordinating site**	
Timing of clinical flow				**X**	
Standard imaging				**X**	
CBCT imaging				**Up to three times per patient**	
Therapist satisfaction				**Last week of RT, or for five-day fractionation, last day of RT**	

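### The questionnaire that defines the primary endpoint has two incompatible schedules, and its seven-week window leaves under two weeks of follow-up after 28 fractions

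*Protocol article*

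**What the plan says.** **Endpoint.** Under Primary endpoint and measures, MD in the fold is positive when the patient answers yes to open skin in the past seven days (Question 7a) and gives a non-zero answer for the area under the breast (Question 7b), unless a blinded assessor definitively rules it out. In that definition staff can remove a positive but cannot create one.

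**Schedule in the text.** Patient population requires seven weeks of participation from RT start, "with PRO questionnaires to be completed weekly, starting the last week of treatment" and continuing to the end of that period. The secondary-endpoint section on patient-reported outcomes has the form given "by the study radiation therapist on the days that the patient is being assessed and by e-mail post-RT". Staff skin assessments requires those assessments only at baseline and in the last treatment week (the last day for five fractions), with later weekly ones optional. These two sections fit the last-week reading.

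**Schedule in Table 1.** The PRO row is marked before the first treatment, under "Weekly during Breast RT", and under "Post-RT weekly to 7 weeks from start of breast RT". In the during-RT column the staff skin-assessment and therapist-satisfaction rows are restricted to the last week; the PRO row is not. The text with the table adds that "A PRO questionnaire is also collected at baseline".

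**Treatment length.** Radiation therapy permits 5, 15, 16 or 25 fractions, the longest option being "50 Gy in 25 or 28 daily fractions". Extended schedules are generally kept for large separation (over 24 cm) or significant post-operative changes.

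**The protocol's own benchmark.** The Background notes, for standard fractionation schedules, that "many studies do not monitor skin toxicity out to two weeks post-treatment when at least 10% of skin reactions peak", and says this can lead to under-reporting of MD.

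**The concern.** A site cannot follow both schedules. Because Question 7a looks back only seven days, the number and timing of forms decide which episodes of open skin can be scored. Open skin early in a long course would be scored under Table 1, but under the text only if it were still present within the look-back of the first last-week form.

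The schedule may also affect the denominator. Statistical methods – primary outcome excludes patients who neither complete all follow-up nor report MD. Participant withdrawal defines completion as all study phases, including treatment and the final questionnaire. Whether a missed form during RT makes follow-up incomplete therefore depends on which schedule is in force.

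The end of the window is a separate matter. It is tied to the start of RT, so observation after RT shrinks as the course lengthens. The longest courses go largely to patients with large separation, which the Background lists among the features of the highest-risk group.

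**Working it through.** **1. Forms per patient.** Assumptions: five weekday fractions per week (the protocol says only daily), no interruptions, first fraction on day 0. With N fractions and start weekday s (Monday = 0, Friday = 4), the last fraction falls on day

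L = (N − 1) + 2 × floor[(s + N − 1)/5].

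The last treatment week is w = floor(L/7) + 1. Weekly forms from week w to week 7 number 8 − w.

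| Fractions | L (day) | w | Forms, text | Forms, Table 1 | Days after RT at day 49 (49 − L) |
|---|---|---|---|---|---|
| 5 | 4–6 | 1 | 7 | about 7 | 43–45 |
| 15 | 18–20 | 3 | 5 | about 7 | 29–31 |
| 16 | 21 | 4 | 4 | about 7 | 28 |
| 25 | 32–34 | 5 | 3 | about 7 | 15–17 |
| 28 | 37–39 | 6 | 2 | about 7 | 10–12 |

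The baseline form is extra in every row.

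**2. Shortfall after 28 fractions.**
- Start Monday to Wednesday: L = 27 + 2 × 5 = 37, leaving 49 − 37 = 12 days, 2 short of 14.
- Start Thursday or Friday: L = 27 + 2 × 6 = 39, leaving 10 days, 4 short.

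Holidays or interruptions would widen the gap. Only 28 fractions falls below 14 days; 25 fractions clears it narrowly. Two weeks of cover after 28 fractions needs follow-up to day 51 (37 + 14) or day 53 (39 + 14). One more weekly form at day 56 would give 17 to 19 days.

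**3. The plan's sample size.** For 50% versus 30%, two-sided α = 0.05 and 80% power, pooled variance and no continuity correction:

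n = [1.960 × √(2 × 0.4 × 0.6) + 0.842 × √(0.5 × 0.5 + 0.3 × 0.7)]² / 0.2² = 93 per arm,

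which reproduces the stated figure. Allowing for 10% loss gives 93/0.9, or 104; the planned 110 leaves 110 × 0.9 = 99 evaluable.

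**4. Illustrative effect on power.** The protocol gives neither the share of patients on 28 fractions nor the share of their MD that a short window would miss. Assume 5% to 50% on 28 fractions and 10% of their MD missed, equally in both arms. Both rates are then multiplied by 1 − share × 0.10.

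| Share on 28 fractions | Observed rates | Power, 93 per arm | Power, 99 per arm |
|---|---|---|---|
| 0% | 50% / 30% | 80.0% | 82.4% |
| 5% | 49.75% / 29.85% | 79.7% | 82.1% |
| 50% | 47.5% / 28.5% | 76.5% | 79.1% |

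The 10% is borrowed for illustration only. In the Background it describes when skin reactions peak, not missed MD.

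**The case against.** **The arms are compared fairly in any case.** A reader might infer that CARA, by reducing separation, moves patients to shorter courses, so that the arms are observed with unequal intensity. The protocol does not say this happens. Randomization is stratified by dose fractionation and takes place before CT simulation, which implies that a schedule is designated before allocation, and the primary model adjusts for fractionation. This objection stands.

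**At least 10% of MD is not shown to fall outside the window.** That reading is tempting but unsupported. The figure concerns peak timing of skin reactions in general, under standard fractionation. The endpoint is any report of open skin, and a reaction peaking at day 14 may already have been open and reported by day 10 to 12. This stands too.

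**Early open skin that heals is hypothetical.** No section says that open skin under the breast appears and resolves well before the last treatment week while irradiation continues. It remains a possibility that the two schedules treat differently, not a demonstrated loss.

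**The shortfall is small.** It is 2 to 4 days, on one schedule of unknown share, under an assumed five-day week. At seven fractions per week it would vanish. That limits its weight but does not remove the mismatch with the protocol's own benchmark. The eight-week limit in Participant withdrawal does not close the gap: it is a rule for unreachable patients and adds no scheduled form.

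None of this answers the contradiction. Table 1 limits neighbouring rows to the last week and leaves the PRO row unlimited, so its mark cannot be read as shorthand for the text.

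**Conclusion.** The contradiction is certain from the text: the questionnaire behind the primary endpoint has two schedules, differing by up to five on-study forms per patient (2 versus about 7 after 28 fractions). It could change which MD is scored and who counts as having completed follow-up.

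The window shortfall is real but modest: 10 to 12 days after 28 fractions, given five fractions per week and no interruptions. The likely consequence is some under-counting of MD in a high-risk subgroup, roughly equal in both arms, with an illustrative power loss of at most about 3.5 points (80.0% to 76.5% at 93 per arm). No between-arm bias is shown. This should be fixed, but it does not undermine the comparison.

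**What to change.** 1. Reconcile Patient population, the secondary-endpoint section on patient-reported outcomes, and Table 1 to one PRO schedule. Weekly throughout RT, as in Table 1, is preferable because it captures MD at any time during the course; the documents themselves establish only that the sections must agree.
2. End PRO follow-up at the later of seven weeks from RT start or at least two weeks after the last whole-breast fraction.
3. Define both the primary endpoint and completion of follow-up over that window, saying whether a missed form during RT makes follow-up incomplete.

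Observation after RT will still be longer for short courses; the change secures a two-week minimum rather than equal follow-up.

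The cost is protocol wording, weekly forms during RT at any site now following the text, and one or two extra e-mailed questionnaires for patients on 28 fractions. Treatment is unaffected. Forms not collected during RT cannot be recovered later, so the correction is worth making promptly.
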